#### Economic End Point

The incremental cost-effectiveness ratio of the pilot program will be assessed by comparing patient health care resource utilization and return to work with matched historical controls [129].

### Timeline

The study timeline is shown in Figure 1. All activities are occurring on track as scheduled. Data collection will be completed by July 2021 and April 2022 for the clinical validation and implementation stages of the project, respectively.

### Recruitment

Patient recruitment began in July 2019. As of December 2019, 71 patients were screened for enrollment, of whom 65 patients met the inclusion and exclusion criteria. Of these, 46 patients consented and 19 declined to participate in the study. Of those recruited, 9 have worker’s compensation claims and 37 do not. Figure 2 shows the recruitment status and patient flow of the ongoing study.

### Data Collection App Details

Data collection is being performed using a custom Android Wear app and the Huawei Watch 2 smart watch. We are collecting 9-axis inertial sensor data and heart rate data during supervised and independent physiotherapy exercises. The sensor data are collected on the smart watch and uploaded to Google Cloud Storage servers. Labeling of the supervised activities is performed in a separate Android app running on an Android tablet (Samsung Tab A) and operated by our research team.

**Figure 1 figure1:**
[figure not shown]
Study timeline. SPARS: Smart Physiotherapy Activity Recognition System.

**Figure 2 figure2:**
[figure not shown]
Recruitment and patient flow as of December 2019.

## Discussion

### Principal Findings

Exercise-based physiotherapy is considered essential in the management of rotator cuff pathology, both as a first-line treatment [4-6] and for postoperative rehabilitation [7,8]. The current paradigm for the delivery of physiotherapy services involves in-person patient assessments and training for prescribed exercise activities, but it requires the patients to perform majority of their exercises independently at home. There is a body of literature that indicates patients often struggle to fully engage in their prescribed activities [9,11], suggesting that many may not receive the full benefit of this important treatment.

A significant barrier to better understanding the impact of this problem on physiotherapy outcomes has been the challenge of accurately assessing adherence to physiotherapy participation in the home setting. This limitation precludes accurate and objective measurement of the administered physiotherapy dose for protocols that include an independent home component.

This manuscript describes a research protocol by which a smart watch and ML approach will be validated for tracking exercise-based shoulder physiotherapy in a cohort of patients with rotator cuff pathology. The validated instrument will also be used in a noninterventional fashion to assess the rate of adherence in the study population, the relationship between adherence and recovery, and patient factors related to physiotherapy adherence. As a final phase of this project, we will pilot an adherence-driven rehabilitation program where real-time measurement of physiotherapy adherence is utilized to promote better patient engagement in their home program.

A smart watch was selected as the platform for physiotherapy adherence tracking chiefly for patient comfort during exercise and ease of use. A significant proportion of the rotator cuff pathology demographic is elderly [16,17] and many have low technology literacy. The smart watch platform we have developed only requires that a patient put on their watch before physiotherapy exercise and that they ensure it is charged before doing so. This is in contrast to other systems that either require multiple sensors to be strapped to various points on the body [70] or a computer vision approach that requires some setup in the exercise environment to obtain and maintain an appropriate field of view [65]. In our setup, raw inertial data are processed using a modern deep learning approach, which we have shown previously to significantly outperform classical algorithms utilizing an engineered feature representation [15]. Although the deep learning approach requires significantly more computing resources for training, the inference time is comparable with classical models and feasible for evaluation either as a cloud service or directly on a patient’s mobile device [15].

There are a number of limitations to the proposed study. In the validation phase of this research, the act of measuring physiotherapy adherence may impact patients’ likelihood of adherence, even in a double-blinded noninterventional fashion, as proposed. Therefore, the assessed adherence rate in the study population may not be generalizable to populations that receive no tracking at all. A further limitation is that the ML algorithms validated in the clinic context will generalize well to the home setting. This risk will be mitigated by assessing algorithm generalization across multiple clinic sessions and to new patients (subject stratification). We assume that if that algorithm generalizes in both these cases, generalization to the home setting is also likely. As we also assess the criterion validity for adherence tracking, a positive relationship between adherence and recovery, if detected, it would serve as further evidence for the validity of algorithm construct.

Despite the efforts we have invested in developing a simple, accurate, and robust method for tracking shoulder physiotherapy, tracking errors will inevitably occur and result in imperfect adherence measurement. These errors could be secondary to software glitches, poor algorithm generalization, accidental or intentional misuse or disuse, hardware failure, and others. Therefore, the adherence estimates that we calculate for each patient will be subject to these errors, which may be random or biased to certain study subjects. To mitigate and assess these effects, we will collect survey data from each patient on their use of the smart watches and ask each patient to manually complete a 2-week adherence diary so that we can compare the measured adherence with patient self-report.

A limitation of the final interventional phase of this study is the pilot sample size (N=20) and the absence of a true control group. Although we can compare the interventional cohort with historical controls in the validation cohort, a better comparison would be with a control group with no tracking at all as per the current standard of care. Ultimately, a larger randomized controlled trial (RCT) would be required to adequately assess the effect of an adherence-driven rehabilitation program on recovery. The pilot study we conduct is primarily powered to detect implementation challenges, refine the system design, and estimate the effect size as required preliminaries to funding and carrying out a larger multicenter RCT.

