### Are Home Shoulder Physiotherapy Exercises Performed Correctly?

Patients with rotator cuff pathology have abnormal shoulder kinematics [53,54]. Due to the weakness of the rotator cuff, these patients develop a functional instability, where shoulder motion reduces the available supraspinatus muscle outlet, causing impingement [55]. There is a known relationship between altered shoulder kinematics, pain, and rotator cuff tear size [56]. It is believed that the altered kinematics and impingement exacerbate the condition, contributing to ongoing deterioration of the rotator cuff [54,55]. Restoration of normal shoulder kinematics, in particular muscular control of the scapula, is a focus of physiotherapy for rotator cuff pathology [19,57], and there are some data that contribute to improved patient outcomes [58]. An important role of the physiotherapist in rotator cuff rehabilitation is to supervise the process of kinematic retraining, ensuring that appropriate muscle recruitment and motion patterns are developed and maintained during exercise [59]. No study has determined whether the motion patterns trained during supervised therapy sessions are maintained in the home setting or independent exercise. The proposed study seeks to establish if there are kinematic differences between supervised and home rotator cuff rehabilitation exercises and determine if there is a relationship between exercise technique and shoulder recovery.

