#### Aim 2: Measure the Rate of Adherence to Home Shoulder Physiotherapy, the Relationship Between Adherence and Recovery, and Identify Barriers to Home Physiotherapy Adherence

##### Objectives

The related objectives are as follows:

Inertial sensor data are collected during home physiotherapy for 120 patients with rotator cuff pathology over full treatment duration (up to 5 months).Technical failures preventing home data collection are less than 5%.Clinical outcomes: return to work status, shoulder range of motion, rotator cuff strength, and patient-reported outcomes of pain and disability are collected pretreatment, monthly through treatment (up to 5 months), and at 12-months final follow-up. The final follow-up exceeds 85%.A total of 23 potentially significant predictors of home physiotherapy adherence (identified in Methods: Barriers to Adherence) are collected for all study participants at the time of recruitment.

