##### Hypotheses

The related hypotheses are as follows:

Exercise technique adherence is better for supervised sessions than at home (*P*<.05).There will be a statistically significant association (*P*<.05) between home physiotherapy exercise participation and technique adherence and the identified clinical outcomes.

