#### Inertial Data Labeling

The researchers will attend a supervised physiotherapy session for each patient once every 2 weeks to record exercise type and technique labels synchronously with inertial data collection, based on the input from the treating physiotherapist. The technique will be labeled as a binary variable, indicating if the treating physiotherapist was satisfied that the exercise was performed correctly (as intended). The treating physiotherapist will also make a record of prescribed home exercises and exercise type and technique evaluations at each supervised physiotherapy session.

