### Data Analysis

#### Sample Size

The proposed sample size of 120 for clinical validation yields a power of 80% to detect weak correlations (*R*>0.25) between physiotherapy adherence and clinical outcomes, accepting a 5% alpha error. Sample size feasibility was confirmed by the WCP, anticipating a recruitment rate of 70%. The pilot study sample size (20) was used to detect implementation challenges with an incidence rate greater than 15% at a 95% confidence level [124] (not statistically significant differences in clinical or economic outcomes).

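### A concurrent link between technique adherence and recovery can arise from severity or recovery itself, so for technique it supports neither algorithm validity nor an effect of adherence

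*Protocol article*

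**What the plan says.** Under Inertial Data Labeling, technique is a binary label, "indicating if the treating physiotherapist was satisfied that the exercise was performed correctly (as intended". A classifier trained on that label then scores home technique (Home Physiotherapy Technique Adherence).

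The Introduction section on whether home exercises are performed correctly attributes abnormal movement to cuff weakness and adds: "There is a known relationship between altered shoulder kinematics, pain, and rotator cuff tear size". The outcomes are work status, pain, DASH, strength and active range of motion (Clinical and Return to Work Outcomes Data).

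The second Aim 2 hypothesis reads "There will be a statistically significant association" and covers both participation and technique. Criterion Validity regresses change in outcome on adherence in univariate linear models. Management type and worker status are moderators, and both concurrent and predictive effects are examined. The abstract's second objective goes beyond association and sets out to determine what effect adherence has on recovery. The Discussion (Principal Findings) states that "a positive relationship between adherence and recovery, if detected, it would serve as further evidence for the validity of algorithm construct".

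**The concern.** The technique label does not separate a patient who ignores the instruction from one who cannot yet make the movement. A weak or painful shoulder may be scored as incorrect, and the same shoulder as correct once it has recovered. In a concurrent analysis, exposure and outcome may then be two readings of the same shoulder. A classifier that detected only weakness or pain would also correlate with recovery, so the correlation does not tell a valid adherence measure from a severity measure.

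This matters most for technique at home. Cross-validation uses supervised sessions. The diary comparison covers number and type of exercises, and technique is compared only with physiotherapist logs. The association with recovery is thus the only planned validity evidence that uses home technique scores, and the Discussion invokes it just after conceding that generalization to the home is assumed. The limitations cover observation effects, generalization and tracking error, but not this one.

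**Working it through.** **1. The protocol's own figure.** Sample Size states: "The proposed sample size of 120 for clinical validation yields a power of 80% to detect weak correlations", with R>0.25 and 5% alpha. By Fisher z, two-sided: power = Φ(√117 × atanh 0.25 − 1.960) = Φ(10.817 × 0.2554 − 1.960) = Φ(0.803) = 78.9%. The noncentral t test of a slope gives 80.1% at N = 120. The figure is sound, and the point does not depend on it. It does show which correlations the study is built to call significant.

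**2. A shared cause, with no adherence effect.** If technique correlates *a* and recovery correlates *b* with a common severity factor, and nothing else links them, they correlate *ab*. With a = b = 0.5 this is 0.25, the correlation the study is powered for. The protocol gives neither *a* nor *b*.

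**3. The planned analysis uses change, so the model must too.** Assumptions, none from the protocol:

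- Capacity C0 at the start and C1 at the end of the interval each have variance 1 and correlate ρ.
- Range of motion = 0.8C + 0.6e at each time.
- Technique has loading k on capacity and no effect on recovery.

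The change D in range of motion has variance 1.28(1−ρ) + 0.72.

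*Technique reflects average capacity.* Cov(C0 + C1, C1 − C0) = 0 when the two variances are equal. So r = 0, and P<.05 occurs in 5% of studies.

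*Technique reflects end-of-interval capacity.* r = 0.8k(1−ρ) / √[1.28(1−ρ) + 0.72]. The chance of two-sided P<.05 at N = 120, by Fisher z:

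| ρ | k = 0.3 | k = 0.5 | k = 0.7 |
|---|---|---|---|
| 0.3 | r 0.13, 30% | r 0.22, 68% | r 0.31, 93% |
| 0.5 | r 0.10, 20% | r 0.17, 47% | r 0.24, 75% |
| 0.7 | r 0.07, 11.5% | r 0.11, 24% | r 0.16, 41% |

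Simulation of three of these cells and of one average-capacity case agreed to within half a percentage point.

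*Technique reflects mid-interval capacity, and patients' gains vary.* With a gain of SD s, independent of starting capacity, r = 0.8ks² / [2√(1 + s²/4) √(0.64s² + 0.72)]. For s = 0.3 to 0.5 the chance is about 5% to 13%. For s = 1.0 it is 17%, 39% and 65% for k = 0.3, 0.5 and 0.7.

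**4. Home technique relative to supervised technique.** With loadings h at home and c in clinic, the difference correlates with the level of range of motion as r = 0.8(h−c) / √[(h−c)² + 2 − h² − c²]. This is 0 when h = c. For h/c = 0.5/0.3, 0.7/0.5 and 0.7/0.3 it is 0.12, 0.14 and 0.25. The contrast removes the overlap only if capacity affects technique equally in both settings.

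**The case against.** Several counter-arguments have force.

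- **The standard is not fixed.** A reader might infer that technique is judged against an absolute standard of movement. The text does not support that: the label is correctness as the treating physiotherapist intended, and the protocol expects the standard to shift through recovery. However, the adaptations it lists (metadata, patient-specific models, retraining) are only possibilities aimed at classifier performance. They lessen the overlap without removing it.
- **Baseline variables are planned.** The abstract promises multivariate analyses with baseline variables, and tear size and symptom duration are collected. This stands, and it answers part of the severity argument. It does not address capacity that changes during treatment, which drives the concurrent analysis.
- **The claim is modest.** The Discussion offers further evidence about adherence in general, behind cross-validation and the diary and log comparisons, and the hypothesis claims only association. That is fair. But the sentence makes no exception for technique, and the abstract's objective speaks of effects.
- **Change scores and timing.** A reader who correlated technique with the level of range of motion (0.8 × 0.3, 0.5 or 0.7 = 0.24, 0.40 or 0.56) would infer spurious significance in 75% to nearly 100% of studies. The planned regression is on change, so those figures do not describe it. Strength and range of motion are also not collected at 12 months, so the most direct overlap lies in the in-treatment data.
- **Harm in the pilot.** One might infer that weak patients will be treated as non-adherent. How adherence informs care is still to be co-designed, so this is a possibility only.

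**Conclusion.** The point holds for technique adherence and the concurrent analysis. A positive technique–recovery association there can come from severity or from recovery itself. It therefore cannot serve as evidence that the technique algorithm is valid or that technique adherence affects recovery.

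The size is uncertain. With no adherence effect, 120 patients and change scores, P<.05 occurs in about 5% of studies if technique reflects average capacity and capacity is equally variable at both times. It occurs in about 11.5% to 93% if technique reflects end-of-interval capacity, for loadings of 0.3 to 0.7 and capacity correlations of 0.3 to 0.7. All these inputs are assumptions, so the range shows what is possible and is not a forecast.

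Two wider readings are not supported. One is that no adherence–recovery association is informative: participation adherence is a share of prescribed exercise and is not scored on movement quality. The other is that home-minus-supervised technique should replace the planned exposure: it depends on equal loadings, and it scores a patient who is wrong in both settings as fully adherent.

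**What to change.** 1. In the Discussion, limit the validity inference to participation adherence, and describe the technique–recovery result as association only. Bring the abstract's wording on effects into line for technique.
2. For technique, base any statement about effect on the predictive analysis, not the concurrent one. Relate technique in an earlier interval to later outcome change, adjusted for outcome status at the start of that interval and for the baseline severity variables already collected.
3. Add home technique relative to the same patient's supervised technique, for the same exercises and two-week interval, as a sensitivity analysis. State the equal-loading assumption beside it.

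No new data are needed: SPARS is to score home sessions and supervised sessions without synchronous labels, and the first Aim 2 hypothesis already compares the two settings. The cost is a noisier secondary estimate and a less favourable validity claim. The predictive analysis remains observational, so confounding by unmeasured severity cannot be excluded.

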### Conclusions

This protocol paper describes a peer-reviewed, grant-funded study to validate a smart watch and ML approach to assess patient adherence to exercise-based shoulder physiotherapy in a population with rotator cuff pathology. This study will provide new and important insights into shoulder physiotherapy adherence, the relationship between adherence and recovery, barriers to better adherence, and methods for addressing them. The ultimate goal of this work is to improve physiotherapy delivery and outcomes for patients with musculoskeletal injuries and disorders.

## Appendix

Multimedia Appendix 1 Peer review reports from Collaborative Health Research Projects - NSERC Partnered.

## Abbreviations

ANN: artificial neural networks
CRNN: convolutional recurrent neural network
DASH: Disabilities of the Arm, Shoulder, and Hand
IMU: inertial measurement unit
ML: machine learning
NPRS: Numeric Pain Rating Scale
RCT: randomized controlled trial
SPARS: Smart Physiotherapy Activity Recognition System
WCP: Working Conditions Program
WSIB: Workplace Safety and Insurance Board
